### Ethics

To protect the legitimate rights and interests of all our project participants, we will apply for a clinical research ethics review. This study has been approved by the Ethics Committee of the First Affiliated Hospital of Hunan University of Chinese Medicine (HN-LL-KY-2020-020-01).

### Protocol amendments

Any significant protocol revisions will be submitted to the Ethics Committee of the First Affiliated Hospital of Hunan University of Chinese Medicine for approval. After obtaining approval, the changes will be updated on *CHICTR*.

### Ancillary and post-trial care

Tuina is a safe and effective intervention with low probability of AEs, but accidents might occur during the study. If a child with ASD encounters an adverse event during the trial, we will report it to the ethics committee of the First Affiliated Hospital of Hunan University of Chinese Medicine, and a committee of medical experts will determine whether the adverse event is related to the trial. We will also provide treatment costs and financial compensation for study-related injuries based on the actual situation.

#### Dissemination policy

The results of this study will be disseminated in multiple formats after statistical analysis. They will be published in advanced peer-reviewed journals related to ASD, TCM, or complementary alternative medicine research, or in the form of scholarly reports.

## Discussion

ASD development is irreversible, with some symptoms persisting throughout life. Given that improving the quality of life of children with ASD is the common pursuit of all treatments, we should actively explore traditional and non-traditional alternatives to identify the most suitable treatment for ASD.

TCM contains profound wisdom from Chinese philosophy and medical knowledge. Consistent with modern medicine, TCM considers the brain to control emotions, consciousness, and thinking. However, in this theory, the brain is not just the organ in charge of those capabilities, as it has several other functions. The cause of autism is related to the brain; this is a consensus in academic circles. Specific acupoints can improve brain function and promote nerve development. *Du Meridian* is a special meridian closely associated with the physical location and function of the brain [33]. A large part of the *Du Meridian* is located on the midline of the back and front of the head; further, it is directly connected to the brain and gathers the Yang qi of the whole body. *Du Meridian* is an important channel for the output of Jing qi [34], as it serves as a bridge between the brain and other meridians for communicating qi and blood [35]. Therefore, the normal operation of the function of the *Du Meridian* can improve the role of the brain; further, children with ASD have problems with obstruction. In such cases, external stimulation can be performed through Tuina. The formulation of this study protocol will be conducted under the guidance of the *Du Meridian*.

The acupoints and treatment plan for Tuina will be based on TCM. There are several fixed routines in Chinese pediatric Tuina, including starting from the head, which is known as Kaiqiao, for unblocking the body. Four fixed acupuncture points will be used in this study: Tianmen, Kangong, Taiyang (Temple), and Wangu (GB12). The number of operations for each acupuncture point is 24, which corresponds to the Chinese 24 solar terms. The *Du Meridian* is also distributed on the head, with the four representative acupoints including Yamen (GV15), Fengfu (GV16), Baihui (GV20), and Shuigou (GV26). Therefore, they were chosen as the main Tuina points. The back, from the thoracic spine to the sacral spine, is the main circulation part of the *Du Meridian* and the main stimulation point. Three methods are used for stimulation: pressing-kneading manipulation, pinching, and pushing with the finger. The last step is grasping Jianjing (GB21), also known as Guanqiao, which relaxes the body.

However, the efficacy of Tuina in ASD treatment requires further investigation. This clinical randomized controlled trial will compare the effects of Tuina combined with behavioral and single education interventions on the rehabilitation of children with ASD. The CARS will be used to evaluate its efficacy, although our goal is to improve the core ASD symptoms in children, including the improvement of intestinal symptoms. This research plan could help build a strong basis for the application of Tuina therapy for children with ASD, which could allow more patients to benefit from this treatment.

## Study limitations

First, the diagnosis of ASD will not be made using the Autism Diagnostic Interview-Revised or Autism Diagnostic Observation Scale due to copyright restrictions; instead, the DSM-5 will be used.

Regarding the evaluation, there are no objective biomarkers for evaluating the efficacy of ASD treatments. This study will employ a scale to evaluate the efficacy of the ASD treatment, which may lead to subjective errors.

Additionally, it is impossible to blindly perform Tuina therapy. Furthermore, the standardization of Tuina techniques and stimulation amount varies from person to person. There will inevitably be some differences in specific operations. To reduce such errors, only Tuina therapists with rigorous training and professional qualifications will participate in the study to ensure standard treatment.

Finally, given the ethical requirements, it is not possible to prohibit all children from participating in other educational or behavioral interventions. Therefore, a single Tuina intervention trial is insufficient to evaluate its feasibility for clinical application.

## Trial status

The recruitment of patients for this clinical trial, which started in November 2020 and ended in September 2021, it is now entering the clinical intervention phase. The trial was registered in the Chinese Clinical Trial Registry on 28 November 2020 (registration number: ChiCTR2000040452).

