**Methods:**

Eligible children will be randomly assigned to either the pediatric Tuina plus conventional treatment group or to the conventional treatment alone group based on a random table at a ratio of 1:1. The effectiveness of the Tuina intervention for ASD will be evaluated by a third-party organization. The pre- and post-intervention scores on the Childhood Autism Rating Scale comprised the primary outcome, whereas pre- and post-intervention scores on the Autism Treatment Evaluation Checklist were the secondary outcomes to assess improvement in symptoms. Baseline values of the participants will be determined at the time of registration. Outcomes will be evaluated after the 30th treatment session. The follow-up period will last for 6 months after treatment.

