## Methods/design

### Study design

This will be a randomized controlled trial. To meet ethical requirements and considering the particularity of ASD, this study will not employ a blind design. The trial will be conducted at Hunan University of Chinese Medicine, China, from November 2020 to December 2022. Eligible children will be randomly divided into the pediatric Tuina plus conventional treatment group or the conventional treatment group based on a computer-generated random table at a ratio of 1:1. Efficacy will be assessed using the Childhood Autism Rating Scale (CARS) and the Autism Treatment Evaluation Checklist (ATEC). Before study commencement, all participants will be assessed using a scale by a third party not involved in the study. The baseline level of the participants will be determined at the time of enrollment; further, the participants will be evaluated again after the 30th treatment, with a follow-up period of 6 months postoperatively. Figure 1 shows the flowchart of the study.

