#### Tuina group

The Tuina group will receive a total of 30 sessions of pediatric Tuina (five sessions per week for 6 weeks, and a follow-up session at the 12th week after the end of treatment). From the perspective of humanistic care, to make the child feel safe, the child will be held by the parents or relatives during the session and placed in a sitting position. Tuina will be performed face to face. When performing acupoint Tuina on the back, the child will lie on his parents or relatives in a prone position.

To standardize the Tuina manipulation, only certified Chinese medicine physicians with 3 months of training in Tuina techniques will perform the procedures. The acupoint prescriptions are mainly based on the TCM theory of the relationship between *Du Meridian* and the *Brain*. After gathering clinical evidence and soliciting the opinions of experienced Tuina experts, we have summarized the following acupoints and manipulation times of Tuina. Table 1 presents the detailed information.

**Table 1 Tab1:** Tuina acupoints, manipulation times, and methods

Acuponits	Location	Methods	Times
Tianmen	Located from the middle of the eyebrows to the front hairline in a straight line	Linear-pushing with the finger	24
Kangong	Located on a horizontal line connecting both brows	Wiping with the finger	24
Taiyang (temple)	Flat part at each side of the forehead	Pressing-kneading with the finger	24
Wangu (GB12)	Located in the posterior inferior depression of the mastoid behind the ear and above the attachment of the sternocleidomastoid muscle		24
Yamen (GV15)	Located on the nape, 0.5 Cun above the middle of the posterior hairline, and below the first cervical vertebra.		100
Fengfu (GV16)	Located on the nape, when the posterior hairline is straight up 1 Cun, the extraoccipital protuberance is straight down, and the depression between the trapezius muscles		100
Baihui (GV20)	Located on the head, 5 Cun above the middle of the front hairline.		100
Shuigou (GV26)	Located on the face, at the intersection of the upper 1/3 and middle 1/3 of the sulcus		100
Du Meridian	Located on the midline of the back. Tuina therapy is mainly performed from the thoracic spine to the sacral spine.	Pressing-kneading with the finger	20
		Pinching with the finger	20
		Pushing with the finger	300
Jianjing (GB21)	Located under the spinous process of the seventh cervical vertebra, on the midpoint of the line with the acromion	Grasping with the finger	10

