#### Primary outcomes

The main efficacy score will be based on the CARS, which covers interpersonal relationships, imitation, and other 15 aspects, with a total score of 60 points. Each aspect will be scored using a four-point scale: age-appropriate (score 0), mildly abnormal (score 1), moderately abnormal (score 2), and severely abnormal (score 3). Participants with a score < 30, 30–35, and ≥ 36 are considered as non-autistic, moderately autistic, and severely autistic, respectively. Outcomes will be evaluated after the 30th treatment session. Follow-up efficacy assessment will be performed at 6 months post-treatment. The difference in CARS before and after the intervention will be considered significant, effective, and ineffective if the reduction is greater than 10, 5–10 (inclusive), or less than 5 points, respectively [29]..

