### Allocation

A computer-generated random number table will be used by statisticians otherwise not involved in the study. After completing the basic data assessment of all children with ASD, the children will be randomly assigned to the Tuina and control groups in a 1:1 ratio. The treatment sequences will be provided to each Tuina physician in an opaque envelope, and only the Tuina physician will be aware of the grouping. The third-party assessors as well as the data analysts will not be aware of the treatment allocations.

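### Baseline CARS and ATEC are set at enrolment but treatment begins only after recruitment closed, so before-after change and the response categories may include 0 to about 10 months of pre-treatment change

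*Protocol article*

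**What the plan says.** All of this is in the protocol article.

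- **When baseline is set.** Study design: "The baseline level of the participants will be determined at the time of enrollment". The Methods part of the abstract agrees: "Baseline values of the participants will be determined at the time of registration". Study design also says: "Before study commencement, all participants will be assessed using a scale by a third party not involved in the study". No maximum interval to the first session is given.
- **When children are randomised.** Allocation: "After completing the basic data assessment of all children with ASD, the children will be randomly assigned to the Tuina and control groups".
- **When treatment starts.** Trial status says that recruitment "started in November 2020 and ended in September 2021, it is now entering the clinical intervention phase".
- **How long treatment lasts.** Tuina group: "The Tuina group will receive a total of 30 sessions of pediatric Tuina (five sessions per week for 6 weeks", with one further session later.
- **When the outcome is taken.** Primary outcomes: "Outcomes will be evaluated after the 30th treatment session".
- **How change is classified.** Primary outcomes: "The difference in CARS before and after the intervention will be considered significant, effective, and ineffective" for a CARS reduction above 10, from 5 to 10, or below 5 points.

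The readable text calls for no repeat rating before the first session. Fig. 2, which holds the schedule, is not shown.

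**The concern.** A before-after score is meant to measure change over a 6-week course. If the first rating dates from enrolment, and treatment waits until recruitment has closed, the score measures change since enrolment. For early recruits the wait may be several times longer than the course; for late recruits it is close to nothing.

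These are children aged 2 to 6, recruited mainly from rehabilitation institutions, and Study limitations concedes that other educational or behavioural interventions cannot all be prohibited. CARS may therefore move while they wait. In the initial study quoted under Sample size estimation, the control group itself improved by 4.27 points, which is close to the 5-point threshold.

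At stake are the three response categories, which rest on absolute change, and any claim about improvement over the intervention. The scores used to judge CARS of at least 30 also age during the wait.

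**Working it through.** **1. Length of the wait.** The article gives months, not days, and states no figure for the lag, so there is nothing to reproduce. With 30.4375 days per month:

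- shortest reading, 30 Nov 2020 to 1 Sep 2021: 275 days = 9.0 months
- middle reading, 1 Nov 2020 to 1 Sep 2021: 304 days = 10.0 months
- longest reading, 1 Nov 2020 to 30 Sep 2021: 333 days = 10.9 months

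The maximum lag is thus about 10 months and the minimum about 0. The course adds 42 days, or 1.4 months. The before-after span is then about 1.4 months for the last child enrolled and 10.4 to 12.3 months for the first, or longer if treatment began after September 2021.

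**2. Effect on the comparison of means.** Write the recorded change as D + C, where D is change during the wait and C is change over the course. Randomisation follows the baseline assessment, so D has the same expectation in both arms and cancels from the difference in means.

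**3. Effect on power and categories.** Inputs from Sample size estimation: mean changes 7.5 and 4.27 (difference 3.23), SD 4.43, one-sided α 0.025, and 200 per arm less 10% = 180. Assumptions that are not in the documents: lag uniform on 0 to 10 months, linear drift of r CARS points per month, normal changes.

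- Mean added change = 5r; added SD = 10r/√12; total SD = √(4.43² + (10r)²/12)
- Power = Φ(3.23 / (SD × √(2/180)) − 1.96)
- Share with a reduction of at least 5 = average over t from 0 to 10 of 1 − Φ((5 − m − rt)/4.43), with m = 4.27 or 7.5

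| r (points/month) | mean added | added at 10 months | SD | control ≥5 | Tuina ≥5 | difference |
|---|---|---|---|---|---|---|
| 0 | 0 | 0 | 4.43 | 43.5% | 71.4% | 27.9 |
| 0.1 | 0.5 | 1 | 4.44 | 47.9% | 75.0% | 27.1 |
| 0.25 | 1.25 | 2.5 | 4.49 | 54.6% | 79.8% | 25.2 |
| 0.5 | 2.5 | 5 | 4.66 | 64.8% | 85.8% | 21.0 |
| 1.0 | 5 | 10 | 5.29 | 78.7% | 92.1% | 13.4 |

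Power at 180 per arm is above 0.99 in every row. At r = 1.0, for example, 3.23/(5.29 × 0.1054) − 1.96 = 3.83, which gives 0.9999.

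**4. Direction.** The distortion of the response difference depends on the cut-off. For a reduction above 10 points, the shares without drift are 1 − Φ((10 − 4.27)/4.43) = 9.8% and 1 − Φ((10 − 7.5)/4.43) = 28.6%, a difference of 18.8 points. Adding 2.5 points to every child gives 1 − Φ((10 − 6.77)/4.43) = 23.3% and 1 − Φ(0) = 50.0%, a difference of 26.7 points. The same drift narrows the contrast at 5 points and widens it above 10, while the true mean effect is unchanged.

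**The case against.** The long lag is inferred; the article dates no child's rating and no first session. Trial status is a brief note, not a schedule. Recruitment, as the article describes it, begins with telephoning and contracting institutions, so November 2020 may precede the first CARS rating. The assessment before study commencement, followed by randomisation of all children, could describe a single round close to treatment. Fig. 2 or the full protocol may contain a repeat rating.

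This limits certainty, and it stands to that extent: about 10 months is an upper bound on one reading of the text. It does not remove the point, because two places say outright that baseline is set at enrolment or registration. If a later rating is the real baseline, those two statements need correcting.

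The second objection is that the main analysis is unharmed. The planned comparison is of two independent means by t-test or rank-sum test, drift before randomisation is balanced in expectation, and power hardly moves. The categories are labels for which the article names no test. This stands in full for the mean comparison. It does not rescue the categories or descriptions of change over the intervention.

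Third, the drift rates have no source. That also stands: the table shows how the categories respond to drift, not what will happen.

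Finally, a child who passes age 6 or falls below 30 while waiting breaks no stated criterion, since judging eligibility at enrolment is ordinary practice. Removing such children after allocation would do more harm than the old score does.

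**Conclusion.** The point holds in a limited form. As written, the plan allows the baseline score to be about 0 to about 10 months old at the first session, for a 6-week course. The CARS response categories and any before-after statement would then mix change during the wait with change under treatment, in proportions that differ between children. At an assumed 0.5 points per month, the longest wait alone supplies the 5 points needed to count as effective.

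A reader might go further and infer that the treatment comparison is biased or underpowered, or that early recruits certainly carry a 10-month-old score. The documents support neither. Randomisation after baseline protects the mean difference in expectation, power remains above 0.99 in every case tried, and no individual rating is dated.

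Severity is moderate. The calendar bound rests on the article's own dates read together. The response percentages rest on assumed linear drift, even accrual, normality and the initial study's means and SD.

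**What to change.** 1. **Where still possible**, define the analysis baseline as the third-party CARS and ATEC rating taken in a short, stated window before randomisation and the first session, with a matching date for controls. Do any re-check of eligibility before randomisation only, and remove no randomised child on account of it. Amend the abstract and Study design to match. Cost: one repeat rating for children whose score is old.
2. **Otherwise**, analyse post-treatment CARS with baseline CARS and the enrolment-to-start interval as covariates, and draw no efficacy conclusion from the before-after response categories. Cost: one extra covariate, from dates the trial should already hold.
3. **In either case**, state the date of the baseline rating and report the interval to the first session (or matching date) by arm. This settles whether the lag was long or short.

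Enrolling and starting institution by institution would have avoided the problem, but recruitment has ended and that is no longer available.

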## Data Availability

The results of this trial will be presented in peer-reviewed journals.

## Abbreviations

AE: Adverse event
ADHD: Attention deficit hyperactivity disorder
ASD: Autism spectrum disorder
ATEC: Autism Treatment Evaluation Checklist
CARS: Childhood Autism Rating Scale
DSM-5: Diagnostic and statistical manual of mental disorders
TCM: Traditional Chinese medicine
